**Methods/design:**

90 patients aged between 16 to 60 years, who meet the diagnostic criteria for CFS and have been diagnosed by their medical practitioner, will be randomly recruited into groups consisting of Intermittent exercise, Graded exercise and usual care (Control). The outcomes will be measured pre-study (Week 0) and post-study (Week 13). Primary outcomes are VO_2peak_, anaerobic threshold, peak power, levels of fatigue, immune cell (CD3^+^CD4^+^, CD3^+^CD8^+^, CD19^+^, CD 16^+^CD56^+^) concentrations and activation. Secondary outcomes include onset of secondary CFS symptoms (e.g. fever, swollen lymph nodes), wellness, mood and sleep patterns. Primary analysis will be based on intention to treat using logistic regression models to compare treatments. Quantitative data will be analysed using repeated measures ANOVA with a linear model, and Cohen’s effect size. Qualitative data such as participants’ responses (e.g. changes in mood and other reactions) following the exercise modalities will be read and sections demarcated. A code will be applied to each segment. A prevalence of codes will be considered thematically.

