CFS is often triggered by a severe viral infection, such as Epstein Barr virus [4]. There is also increasing evidence to suggest that CFS is also associated with immune system dysfunction, such as increased inflammatory cytokines and reduced lymphocyte activation [4-7]. CFS can cause severe interruptions to education or employment for patients, and the physical inactivity associated with the syndrome may increase the risk of other chronic conditions such as cardiac disease, metabolic conditions and cancer. Earlier studies found that the majority of individuals with CFS have slight to substantial improvement within 1.5 - 4 years with less than 10% reporting complete recovery [8,9]. Approximately 20-50% of adults with CFS demonstrate some improvement in the condition, although only 6% returned to levels of normal function [10,11]. Rehabilitation is usually slow with symptoms described as fluctuating. Approximately 10% of individuals with CFS may improve for periods of at least a year, with a proportion relapsing intermittently [10,11]. Most patients relate that they never return to their pre-morbid level of health [11,12]. After a period of rest, some individuals may return to work but usually with limited working hours. It is apparent that the combination of tiredness, poor memory and difficulties with concentration are reflected in the changes to their productivity.

CFS patients are often advised to remain as active as possible but patients usually show a range of physiological responses to exercise indicative of fatigue and deconditioning. Such responses include reduced exercise capacity, early onset of anaerobic threshold, increased lactate responses during incremental exercise, increased heart rate responses, and also anomalies within perception of their physical effort such as higher rates of perceived exertion compared to controls [2,13,14]. Hypothalamic, mitochondrial and sympathetic dysfunction may also be implicated in exercise and fatigue responses in CFS patients [3,15,16].

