## Methods

### Design

This study is a randomised controlled trial that will compare the outcomes of a 12-week intermittent cycling exercise program to a graded exercise cycling program and standard care (rest and lifestyle advice). The primary outcomes of the study are aerobic capacity (VO_2peak_), perceived exertion, fatigue, muscle pain, immune cell counts, lymphocyte (CD4^+^, CD8^+^, CD19^+^, CD16^+^56^+^) concentrations and function. Secondary outcomes are wellness indices and physiological adaptations to exercise (changes in heart rate, heart rate variability, blood pressure, body composition, anaerobic threshold) and measures of presence, severity and type of fatigue (mental and physical). Southern Cross University Research Ethics Committee has approved all study procedures (HREC ECN-13-066).

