### Interventions

#### Exercise groups

Participants randomized to the exercise intervention groups will engage in a 12-week exercise program consisting of either intermittent exercise (IE) or graded exercise (GE). The exercise sessions will be group-based and conducted at the Southern Cross University Health Clinic, three times per week. All sessions will be supervised by an accredited Exercise Physiologist (AEP) and post-graduate clinical exercise physiology students. Each exercise session will consist of a 5 minute gentle warm up of unloaded cycling, followed by initially a 10 to 15 minute block of either steady state exercise (GE) or intermittent exercise (IE) at an intensity pre-determined from the baseline VO_2peak_ cycle test for each participant. Depending upon the symptom limits of the exercise, the duration of the exercise block can be gradually increased for each participant as tolerated to either a steady state (constant effort) low-moderate intensity cycling period, (50% VO_2peak_, RPE 3 [0–10 Borg Scale]) initially for 10 minutes (GE group) OR an intermittent exercise block of 1 minute of moderate intensity cycling (60% VO_2peak_, RPE 4–5) alternated with 1 minute of unloaded or very low intensity/unloaded cycling (20-30% VO_2peak_, RPE 1–2), totalling 20 minutes. A cool down of 5 minutes unloaded cycling plus stretching of main muscle groups for both groups is also included in the exercise session.

During the 12 weeks of training, we aim to progress the duration of GE towards 20 min, as tolerated by the participant, and to progress the IE participants towards intervals of 2–3 min of moderate intensity cycling, alternated with 1 minute intervals of low intensity cycling, totalling 25–30 min duration. Resting heart rate, heart rate variability (standard deviation of the normal to normal R-R intervals and the root mean square of differences of successive R-R intervals), resting blood pressure, RPE, (0–10 Borg Scale) and fatigue levels will be recorded prior to, and after, each exercise session. Participants will be asked to record any changes, such as elevated or depressed mood, changes to sleep patterns or general well-being, that they perceive to have occurred during their participation in the exercise training.

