### Outcome measures

All outcome measures will be collected at baseline (Week 0) and after the exercise interventions (Week 13). Trained research personnel blinded to the randomization procedures will conduct the initial participant screenings and baseline assessments, which include a full medical history, resting heart rate, resting blood pressure and anthropometry (height; weight; BMI; waist, hip and limb girths), fatigue severity and wellness questionnaires. The project outcome measures consist of a full cell count; lymphocyte receptor flow cytometric assays; incremental cycling test (VO_2peak,_ anaerobic threshold); spirometry; Personal Well Being Index [33] and Fatigue Severity Scale [34].

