#### Fatigue and muscle pain

RPE and fatigue will be recorded at rest and during the incremental exercise test. Participants will be asked to complete a linear pain scale (0 – 10) to indicate if they have any muscle or joint stiffness or soreness prior to the exercise test, immediately post-exercise and also 24 hours post-exercise test. RPE and pain scales will also be completed at every training session to carefully monitor symptoms. The Fatigue Severity Scale [34] and the Chalder Fatigue Scale [39], both CFS-specific, will be administered pre- and post-study to assess the severity and nature of the fatigue, mental and physical.

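### Each fatigue questionnaire is read once before and once after; a second reading at each end, averaged and baseline-adjusted, would add precision cheaply, by an amount the protocol does not allow us to fix

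*Protocol article*

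**What the plan says.** The Outcome measures section sets the general schedule: "All outcome measures will be collected at baseline (Week 0) and after the exercise interventions (Week 13". Under Fatigue and muscle pain, the Fatigue Severity Scale and Chalder Fatigue Scale, "both CFS-specific, will be administered pre- and post-study to assess the severity and nature of the fatigue, mental and physical". No repeat or averaging is planned at either end.

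Fatigue is also recorded in two other ways. In the exercise arms, "fatigue levels will be recorded prior to, and after, each exercise session". At the exercise tests, "RPE and fatigue will be recorded at rest and during the incremental exercise test".

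Fatigue appears among the primary outcomes in the abstract ("Primary outcomes are VO_2peak_, anaerobic threshold, peak power, levels of fatigue") and in the Design section ("perceived exertion, fatigue, muscle pain, immune cell counts"). The Design section then lists, as secondary, "measures of presence, severity and type of fatigue (mental and physical".

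The Statistical analyses section assigns the fatigue scales to a Kruskal-Wallis test. It does not say whether the test compares change or the scores at each time point, and it mentions no baseline adjustment for these scales. The sample size section is based on VO2peak and gives no SD, reliability, correlation or power for fatigue.

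**The concern.** The Background says of the illness: "Rehabilitation is usually slow with symptoms described as fluctuating". If part of that fluctuation is short-term, a single reading at each end mixes the participant's state on that day with any treatment effect. One reading is natural for an exhaustive exercise test or a blood assay. Short self-completed forms could be repeated with little effort.

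The session-by-session fatigue records do not fill the gap, because control participants attend no sessions. The between-arm comparison on a questionnaire therefore rests on one reading before and one after. The trial's size was not set for fatigue, so repeating the forms is a way to sharpen that comparison without recruiting more patients.

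**Working it through.** **The plan's own figure.** The sample size section states 82% power with 25 per group at alpha 0.05, for VO2peak. It gives no effect size or SD, so the figure cannot be recomputed. Solving backwards, 82% for two arms of 25 corresponds to a difference of 0.83 SD (two-sided t test). This says nothing about fatigue.

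**Inputs.** From the article: 25 per arm, alpha 0.05, one reading at each end. Assumed, because the article gives none of them: the correlation *w* between two readings at the same end, the pre-post correlation *b*, and, for illustration, a true difference of 0.5 SD between two arms, tested two-sided.

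**Formulas.** Set the variance of a single reading to 1. The mean of two readings has variance v = (1 + w)/2, and the covariance between the baseline mean and the follow-up mean is b. Then:

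- Baseline-adjusted, one reading at each end: residual variance 1 − b².
- Baseline-adjusted, two readings at each end: v − b²/v.
- Follow-up scores only: 1 with one reading, v with two.

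**Worked example, w = 0.8, b = 0.6.** v = 0.9. One reading: 1 − 0.36 = 0.64. Two readings: 0.9 − 0.36/0.9 = 0.50. Cut: 1 − 0.50/0.64 = 22%.

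**Range, baseline-adjusted.**

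| w | b | one reading | two readings | cut | power for 0.5 SD |
|---|---|---|---|---|---|
| 0.9 | 0.5 | 0.75 | 0.687 | 8% | 52% to 55% |
| 0.9 | 0.6 | 0.64 | 0.571 | 11% | 58% to 63% |
| 0.8 | 0.5 | 0.75 | 0.622 | 17% | 52% to 59% |
| 0.8 | 0.6 | 0.64 | 0.500 | 22% | 58% to 69% |
| 0.6 | 0.6 | 0.64 | 0.350 | 45% | 58% to 83% |

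The last row is a limiting case: readings taken close together correlate no better than readings 13 weeks apart.

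**Follow-up scores only.** The cut is 1 − v: 5% at w = 0.9, 10% at 0.8, 15% at 0.7 and 20% at 0.6. Treating the comparison as a t test, power for 0.5 SD rises from 41% to between 43% and 49%.

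**Baseline adjustment alone.** If the planned test compares follow-up scores only, adjusting a single follow-up reading for a single baseline reading already takes the variance from 1 to 0.64 at b = 0.6 (41% to 58% power) with no extra form. The two parts of the change should therefore be counted separately.

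**The case against.** The strongest reply is that nothing here is wrong or contradictory: the sections agree on a pre/post schedule, and repeating the forms is a preference. That stands, and the point is offered only as an inexpensive improvement.

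A reader might infer that a cut of 20-45%, and power rising from 58% to 69-83%, can simply be claimed. The documents do not support that:

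- Every correlation is assumed. The 45% end is the limiting case in the table, and stable scores give far less.
- The 58% starting point is for a baseline-adjusted model. The article plans a Kruskal-Wallis test and does not state such a model.
- The Background sentence on fluctuation gives no weekly time scale. It concerns slow rehabilitation, and the text that follows speaks of improvement lasting at least a year. If fluctuation is that slow, same-end readings correlate highly and a second one adds little.

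A reader might also infer that fatigue as a primary outcome rests on one questionnaire. Two scales are used, fatigue is also rated around the exercise test, and the Design section's secondary list nearly describes what these scales measure. Their rank is unclear.

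Two practical objections also stand, and they shape the fix. A Week 12 reading would fall while the exercise arms are still training, and so would mix on-training and post-training fatigue in those arms only. Telephone completion for controls alone would make the mode differ by arm.

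**Conclusion.** The point holds as a modest efficiency gain. The article fixes one questionnaire reading at each end, the session records have no counterpart in controls, and averaging a second reading with baseline adjustment lowered the variance under every correlation tried.

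The size depends on values the article does not give. With a pre-post correlation of 0.5 to 0.6, the cut is about 8-11% at a same-end correlation of 0.9, about 17-22% at 0.8, and about 45% at most. It is about 5-20% if only follow-up scores are compared. No single figure should be quoted without its assumptions. The power figures also assume a 0.5 SD difference, which is illustrative.

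**What to change.** 1. In Outcome measures and in Fatigue and muscle pain, give both scales twice before allocation, on separate days and before the baseline exercise test. Give them twice more after the last training session and before the Week 13 exercise test. Use the same days and the same mode (for example, self-completed paper) in all three arms. Space the paired readings far enough apart to sample short-term fluctuation.
2. In Statistical analyses, compare the arms on the mean follow-up score adjusted for the mean baseline score, with a rank-based analysis of covariance if the scores are clearly non-normal.
3. In Design, reconcile fatigue as a primary outcome with fatigue severity and type as secondary, and say where these two scales belong.

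Cost: two extra completions of two short forms per participant (2 × 2 × 90 = 360 forms), a slightly tighter schedule between the last session and the Week 13 test, and a minor amendment. The article does not cost this. It also does not say whether screening and baseline fall on separate days, so the first baseline form may have to be completed at home.

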#### Wellness indices

Quality of life and wellness will be assessed pre- and post-study using the Personal Well Being Index, [33] and the Revised Clinical Interview Schedule medical history [40].

### Statistical analyses

Primary analysis will be via intention-to-treat with all patients included regardless of dropout or level of adherence. Missing data will be imputed according to the maximum likelihood expectation algorithm via the Statistical Package for the Social Sciences (SPSS© Version 19.0). Physiological and exercise test data will be presented as the mean ± standard deviation, with confidence intervals used to express group differences. Changes between groups and the time effect for each group will be determined by repeated measures analysis of variance with a Bonferroni adjustment for significant differences between groups. Cohen’s Effect sizes and 90% confidence intervals will be calculated, to utilise a magnitude-based approach to inferences [41], with the following descriptors applied: (1) Effect size thresholds: <0.2 trivial, <0.6 small, <1.2 moderate, <2.0 large, <4.0 very large, >4.0 extremely large, and (2) Thresholds for assigning qualitative terms to chances of substantial effects: <0.5%, almost certainly not; <5.0%, very unlikely; <25%, unlikely; <75%, possible; >75%, likely; >95%, very likely; >99.5%, almost certain. An effect is unclear if its confidence interval includes both substantial increases and decreases [41]. A p value of < 0.05 will be considered indicative of statistical significance; clinical significance will be interpreted in light of the meaningfulness and magnitude of the adaptations observed. Data from linear pain scales will be recorded pre- and post-study, and reported as frequencies of scores between 0 and 10. Data will then be analysed using ANOVA (group and time effects). Data from wellness indices will be recorded pre and post, combined into domains and a representative total score from the time points analysed using an ANOVA. Data (non parametric) from the Fatigue scales, also measured at time points, will be collated and analysed using a Kruskall-Wallis test.

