### Sample size and power calculation

A previous exercise intervention study provided VO_2peak_ data from a CFS sedentary, age-matched cohort (16.2±1.3 yr) [18]. This data has been used to compute statistical power *a priori* using the non-commercial statistical power analysis program G*Power. The control group is expected to experience no change in the aerobic capacity after 12-weeks while the intervention groups are expected to increase this measure following the exercise interventions. Setting an alpha level of 0.05, approximately 75 participants (25 per group) will provide 82% power to detect a statistically significant difference between groups. Recruitment will be inflated to 90 participants to enable a 20% participant attrition rate.

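### EM imputation followed by ordinary ANOVA counts filled-in Week 13 values as observed, so standard errors are too small or the treatment effect is diluted

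*Protocol article*

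**What the plan says.** The Statistical analyses section of the protocol article fixes three steps:

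- **Analysis set:** "Primary analysis will be via intention-to-treat with all patients included regardless of dropout or level of adherence".
- **Missing values:** "Missing data will be imputed according to the maximum likelihood expectation algorithm via the Statistical Package for the Social Sciences" (version 19.0). The name of the algorithm is not standard, but expectation-maximisation (EM) is the natural reading.
- **Test:** "repeated measures analysis of variance with a Bonferroni adjustment for significant differences between groups". The pain and wellness scores also go to ANOVA, and the fatigue scales go to a Kruskal-Wallis test.

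The section mentions no multiple imputation, number of completed data sets, pooling rule or variance correction. It does not say whether treatment group enters the imputation model.

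Two other sections matter. Under Outcome measures, outcomes are collected only at Week 0 and Week 13. Under Sample size and power calculation, 90 are recruited "to enable a 20% participant attrition rate".

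**The concern.** EM is a sound way to estimate means and covariances when data are missing at random. The trouble starts when its predictions are written into the data set and an ordinary ANOVA is run on the result. Each prediction lies on the regression line, so it adds a participant to the degrees of freedom but no residual scatter. No term reflects the uncertainty of the prediction.

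The consequence depends on a choice the article leaves open:

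- **Group in the imputation model:** the estimated difference is right on average, but its standard error is too small.
- **Group left out:** missing values in every arm are drawn from one common line, so the arms are pulled together and the difference shrinks.

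Either way, the primary intention-to-treat result is wrong in its p-value or in its estimate. The 90% confidence intervals and the likelihood labels of the magnitude-based approach rest on the same quantities and inherit the error.

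**Working it through.** **Inputs from the article.** Three groups; 90 recruited, so 30 per group; two time points; alpha 0.05; 20% attrition. Baseline testing precedes allocation (Participants), so missing values fall at Week 13. At 20%, 0.20 × 90 = 18 values are imputed and 72 are observed.

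**Assumptions, because the article gives no figures.** Baseline to Week 13 correlation ρ of 0.5 to 0.9; fraction missing m of 10% to 30%; values missing completely at random and equally across arms; outcome SD of 1.

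**The plan's own figure.** The article gives no error rate for its imputation. Its one related figure, "approximately 75 participants (25 per group) will provide 82% power to detect a statistically significant difference between groups", cannot be reproduced because no effect size or SD is stated. The check below does not depend on it.

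**Approximation, group in the model.** With only Week 13 missing, EM equals regression of Week 13 on baseline in the observed cases. Per participant, the variance of change that the ANOVA sees is (1−ρ)² + (1−m)(1−ρ²). The variance that governs the group mean is (1−ρ)² + (1−ρ²)/(1−m), ignoring error in the slope. Their ratio is r², and r is the reported over the true standard error. In large samples the 2-df test at nominal 5% rejects with probability 0.05 raised to the power r². For m = 0.20:

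- ρ = 0.5: r² = (0.25 + 0.60)/(0.25 + 0.9375) = 0.716, r = 0.85, rejection 11.7%.
- ρ = 0.7: r² = (0.09 + 0.408)/(0.09 + 0.6375) = 0.685, r = 0.83, rejection 12.9%.
- ρ = 0.9: r² = (0.01 + 0.152)/(0.01 + 0.2375) = 0.655, r = 0.81, rejection 14.1%.

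**Approximation, group left out.** A fraction m of each arm is given values with no group difference, so the expected difference is (1−m) × δ. For m = 0.20 and δ = 0.50 this is 0.40.

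**Simulation.** 30 per arm, ANOVA on change (with two time points this equals the group-by-time test), 4000 trials under the null and 2000 with a 0.50 SD effect in both exercise arms. Ranges are over ρ = 0.5, 0.7, 0.9.

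| Missing | Analysis | Reported SE / true SE | Type I error | Estimate of 0.50 |
|---|---|---|---|---|
| 10% | Observed data only | 0.98–1.00 | 4.7–5.2% | 0.49–0.50 |
| 10% | EM, group in | 0.91–0.93 | 8.0–8.3% | 0.50–0.51 |
| 10% | EM, group out | 0.99–1.01 | 4.3–5.6% | 0.45 |
| 20% | Observed data only | 0.98–1.01 | 4.4–5.1% | 0.49–0.50 |
| 20% | EM, group in | 0.80–0.84 | 12.5–14.0% | 0.49–0.50 |
| 20% | EM, group out | 0.99–1.01 | 4.5–5.4% | 0.40 |
| 30% | Observed data only | 0.99–1.00 | 4.9–5.3% | 0.49–0.50 |
| 30% | EM, group in | 0.71–0.77 | 17.3–21.7% | 0.50–0.51 |
| 30% | EM, group out | 0.98–0.99 | 4.9–5.2% | 0.35 |

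A second set of runs (4000 trials per setting, ρ of 0.5 to 0.8, true effect 0.60 SD) agrees. At 20% missing, type I error by group was 12.2%, 13.5% and 13.3%, and pooled imputation gave 0.474 to 0.483.

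**Effect on the 90% intervals.** With group in the model and r of 0.80 to 0.84, actual coverage is about 2Φ(1.645r) − 1. That is 2Φ(1.316) − 1 = 81% to 2Φ(1.382) − 1 = 83%.

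**The case against.** The strongest reply is that the harm is conditional. The article does not say that imputation is single, that no residual is added, or whether group is in the model, and a fuller plan might settle these. The two harms are also alternatives: when group is left out, the test keeps its level. This stands as a limit on what can be claimed, and neither harm should be stated as certain. It does not rescue the sentence, because the method is stated, no pooling step follows, and both readings fail. Adding one random residual to each imputed value does not cure it either: with group in the model and 20% missing, type I error was still about 11% to 12%.

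Other points carry some weight:

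- **Standardised effects shrink less than raw ones.** Pooled imputation also reduces the SD. In units of the change-score SD, the dilution at 20% missing is about 13% (0.60 to 0.52 at ρ = 0.5; 0.95 to 0.83 at ρ = 0.8). The raw difference still loses about 20%.
- **20% is a planning allowance.** People who stop training could still be tested at Week 13. At 10% missing the damage is smaller but present.
- **Session data might inform the imputation.** Heart rate, exertion, fatigue and pain are recorded at training sessions. These exist only for the exercise arms, do not include peak oxygen uptake, and are not named as imputation variables.
- **The abstract calls this a pilot.** That bears on urgency. The Statistical analyses section still sets significance at p below 0.05, and the Discussion presents the results as evidence for best practice.

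**Conclusion.** The concern holds. As written, the missing-data rule combined with ordinary ANOVA gives a wrong primary analysis. At the article's own 20% attrition, either the false-positive rate is about 12% to 14% instead of 5%, with standard errors 16% to 20% too small, or the raw treatment difference is understated by about 20%. At 10% missing the corresponding figures are about 8% and 10%.

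These sizes assume loss that is completely random and equal across arms, a baseline to Week 13 correlation between 0.5 and 0.9, and EM used as a single fill-in. Actual attrition changes the size, not the direction. The Kruskal-Wallis test for the fatigue scales was not simulated. There too, filled-in scores would be counted as observed.

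**What to change.** Replace the imputation sentence. The preferred wording is that all randomised participants are analysed with a likelihood-based linear mixed model of the baseline and Week 13 values, with group, time, group by time, gender and age stratum, and no imputation. This can be run with the MIXED procedure in SPSS 19. It uses the dropouts' baseline values and is valid when data are missing at random given what was observed. The reference analysis in the table is ANOVA on observed change; the mixed model itself was not simulated.

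An acceptable alternative is multiple imputation with at least 20 data sets, treatment group in the imputation model, and results combined by Rubin's rules. Under either option the fatigue scales need their own sentence, since they are now routed to a rank test on completed data.

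The cost is a change of wording and minor programming in the same software. Visits, participants and sample size are unaffected. Intervals will be wider than under the present plan, because they will reflect about 72 rather than 90 measured Week 13 values if attrition reaches 20%.

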Strategies to manage CFS include pharmacology, physical activity where appropriate (for example graded exercise (GE) and pacing), and psychological approaches such as cognitive behavioural therapy (CBT) which seek to modify behaviour, beliefs and coping strategies. [17-20]. Current best practice for the physical training of CFS patients involves GE sessions where the patient exercises at a well-tolerated constant rate or load (steady state), and the duration of the exercise session is gradually increased over time [2,18-20]. CBT is usually combined with exercise management [18,20].

Evidence of the efficacy of GE, CBT, pacing and other prescriptions of physical activity has been mixed. Some CFS patients still report symptom exacerbation and muscle pain with GE, and consequently are less likely to be physically active [21,22]. Yet other studies have reported that aerobic and resistance exercise improves aerobic capacity and strength [13], fatigue [17], profile of mood states and inflammatory cytokines [14,17,21,23-26].

Intermittent training, where intervals of exercise are alternated with intervals of rest or very low intensity exercise, has been used with cardiac [27], pulmonary [28,29], cancer [30] and older clients who are very deconditioned [31]. Clapp et al. (1999) reported that an acute session of intermittent exercise for 30 minutes did not exacerbate CFS symptoms immediately post-exercise, or for up to 7 days post exercise [32]. In CFS patients, intermittent training may increase exercise tolerance by decreasing perceived exertion, and delaying the onset of fatigue and muscle pain, whilst still providing the same total amount of physical activity as GE. Patients may find it easier to adhere to an intermittent exercise programme if their symptoms are not exacerbated, and therefore may improve their health.

Study hypotheses and aims: the primary aim of the trial is to investigate the efficacy of 12 weeks of intermittent or graded exercise on aerobic capacity, fatigue, immune function and wellness in CFS patients compared to standard care (typically rest, pharmacology and advice about physical activity). We hypothesise that:

1) Both exercise interventions will improve exercise tolerance, aerobic capacity and wellness compared to the control condition, and

2) IE will result in greater exercise tolerance, less fatigue and other symptoms, improved immune function and better exercise adherence compared to GE.

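### For outcomes analysed by repeated measures ANOVA, the plan tests each arm's change over time alongside the between-arm comparison and does not make the within-arm test subordinate

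*Protocol article*

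**What the plan says.** In the protocol article, Statistical analyses, directly after the sentence on physiological and exercise-test data: "Changes between groups and the time effect for each group will be determined by repeated measures analysis of variance", continuing "with a Bonferroni adjustment for significant differences between groups". The sentence therefore plans two inferences, and the multiplicity adjustment is attached to one of them. Later in the same section: "A p value of < 0.05 will be considered indicative of statistical significance". That threshold is general. It is not limited to the between-arm tests, nor is it stated for the within-arm tests in particular.

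The trial's questions are comparative. Hypothesis 1 in the Background reads "Both exercise interventions will improve exercise tolerance, aerobic capacity and wellness compared to the control condition", and hypothesis 2 sets intermittent exercise (IE) against graded exercise (GE). The Sample size section says that 25 per group "will provide 82% power to detect a statistically significant difference between groups".

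The same section sends other outcomes to other methods: the fatigue scales to a Kruskal-Wallis test, and the pain scales and wellness indices to separately described ANOVAs. None of those sentences states a time test for each arm.

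**The concern.** A pre-post test within one arm asks whether that arm changed. Its answer mixes any exercise effect with natural course, regression to the mean and familiarity with the test, which the randomised control arm is there to remove. Finding a significant change in IE and none in control is not a test of IE against control, and a significant change in IE but not in GE is not a test of IE against GE.

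For one outcome the within-arm and between-arm results can point in different directions. The wording leaves room to report an exercise arm as significantly improved when it did no better than control. The trial is meant to inform best practice in CFS, so such a statement would carry weight.

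**Working it through.** **The plan's own figure.** The 82% power for 25 per group at alpha 0.05 cannot be recomputed, because the article gives no effect size, SD or test family. Solving back, it implies Cohen's f = 0.375 for a one-way ANOVA on 75 participants, or a standardised difference of about 0.81 to 0.83 for one two-arm comparison. The figure refers to a between-group difference and says nothing about the within-arm tests. Nothing below depends on it.

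**Inputs.**
- 25 per arm (Sample size section). 30 per arm is also shown, since 90 are recruited and all are to be analysed.
- Significance level 0.05 (Statistical analyses), taken as two-sided because the sidedness is not stated.
- Two measurement times, Week 0 and Week 13 (Outcome measures), so the time effect in one arm is a paired comparison.
- Assumption: all three arms share the same true change d, in SDs of the change score, and there is no treatment effect. The article gives no value for d, so a range is used.

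**Step 1: no change in any arm (d = 0).** A two-sided 0.05 test gives a false improvement with probability 0.025. For at least one of the two exercise arms: 1 − 0.975² = 0.049, about 5%.

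**Step 2: shared change.** Per-arm power p comes from the noncentral t distribution with n − 1 degrees of freedom and noncentrality d√n. For n = 25 the noncentrality is 1.0, 1.5, 2.0 and 2.5 at d = 0.2, 0.3, 0.4 and 0.5. The arms are independent, so:
- P(at least one exercise arm significant, control not) = [1 − (1 − p)²] × (1 − p)
- P(exactly one of IE and GE significant) = 2p(1 − p)

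| d | p (n = 25) | exercise significant, control not | exactly one of IE and GE |
|---|---|---|---|
| 0.2 | 0.161 | 0.296 × 0.839 = 25% | 27% |
| 0.3 | 0.302 | 0.513 × 0.698 = 36% | 42% |
| 0.4 | 0.484 | 0.734 × 0.516 = 38% | 50% |
| 0.5 | 0.670 | 0.891 × 0.330 = 29% | 44% |

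A simulation of 200,000 trials, counting improvements only, gives 24.7%, 35.8%, 37.7% and 29.5% for the third column. At 30 per arm it gives 27%, 38%, 35% and 23%.

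The pattern becomes rarer for larger shared changes (17% at 0.6 SD and 3% at 0.8 SD, n = 25), because control then becomes significant too. The chance that at least one exercise arm is significant, whatever control does, keeps rising: 29%, 51%, 73% and 89% at 0.2 to 0.5 SD.

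**Step 3: the between-arm test on the same simulated data.** With pairwise contrasts of change at 0.05/3, an exercise arm is falsely declared better than control in about 1.5% of trials, and any false pairwise difference appears in about 4.3%. Neither depends materially on d, because a shared change cancels from the difference.

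**The case against.** The article never says that efficacy will be concluded from within-arm tests. The sentence names changes between groups first, confidence intervals are to express group differences, the Abstract describes the primary analysis as one that compares treatments, and the hypotheses and power statement are between-arm. A condensed article may also leave the ranking of tests to a fuller document. This stands as a limit: the randomised comparison is planned, and the 25% to 38% is the probability of a data pattern. It becomes an error rate only if someone infers efficacy from that pattern. It does not remove the point, because the article itself states the per-arm time effect, under a threshold that does not exclude it.

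Three stronger readings are tempting and are not supported.

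- A reader might compute 1 − 0.95³ = 14.3% for three unadjusted within-arm tests and call it the false-positive rate. That figure includes the control arm and significant deterioration. For a false improvement in an exercise arm the figure is about 5%. Extending Bonferroni to the within-arm tests would not help either, because they address the wrong contrast.
- A reader might take "Approximately 20-50% of adults with CFS demonstrate some improvement in the condition" as evidence of improvement during the trial. The sentence gives no time frame or outcome measure, and a neighbouring sentence speaks of 1.5 to 4 years. For aerobic capacity, the Sample size section expects no change in controls. A shared change is plausible, but its size is not documented.
- A reader might apply the risk to every outcome. Fatigue, pain and wellness have their own stated analyses, with no per-arm time test named.

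**Conclusion.** The point holds for the data analysed by repeated measures ANOVA, which means at least the physiological and exercise-test outcomes. There the plan includes a significance test of each arm's change that answers neither hypothesis, and nothing in the wording subordinates it to the between-arm comparison.

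If efficacy were read from those tests with no treatment effect, the misleading pattern would arise in about 25% to 38% of trials at 25 per arm (23% to 38% at 30 per arm), given a shared change of 0.2 to 0.5 SD of the change score. With no change anywhere, the chance of a false exercise-arm improvement is about 5%. These figures are per outcome and assume independent arms, normally distributed changes and two-sided tests. The shared change is an assumption throughout.

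This is a flaw of interpretation that one change of wording removes. The planned between-arm comparison, the data and the sample size are unaffected.

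**What to change.** In Statistical analyses, state that efficacy conclusions rest on the between-arm difference in change: the group-by-time effect, with the planned Bonferroni-adjusted contrasts of IE with control, GE with control and IE with GE. Replace the test of the time effect in each group with a descriptive report of each arm's mean change and its confidence interval, without a significance test.

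The cost is a sentence or two of wording, with no extra patients, visits or data. The small downside is that within-arm p values can no longer be cited as evidence of benefit.
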